### Primary and Secondary Outcome Measures

#### RRV of Food

The RRV of food will be measured by a validated behavioral choice questionnaire that asks participants to make a choice between receiving the food they rated as their most liked (ie, nacho cheese–flavored tortilla chips, original potato chips, candy bars, or chocolate chip cookies) and receiving money [60]. To determine how reinforcing food is in comparison with money, the behavioral choice questionnaire provides participants with 16 different choices, in which they make a choice between receiving the most liked food (100 kcal serving) and receiving the money (US $0.25). Each choice—food or money—is associated with a different number of button presses (using a tally clicker) required to gain access to the choice. Each of the 16 choices on the questionnaire requires the same number of button presses (ie, 20) for the money, whereas the number of button presses for the food increases with each choice. Choice 1 begins with 20 button presses for either the money or the food. The number of button presses required to receive the food increases in 20 response increments for choices 2 through 16. Thus, by choice 16, participants could have access to the food if they are willing to make 320 presses or receive the money for 20 presses. Participants will select whether they want money or food for choices 1 through 16. To produce valid responses, participants will be informed that they will be performing one of their choices by choosing 1 of 16 numbers from a hat, with the numbers representing the choice from the questionnaire (eg, if a participant randomly selects number 6, the participant will carry out the decision made for choice 6, which is either 120 button presses for the most liked food or 20 button presses for the money). After participants complete the number of button presses associated with the choice drawn, they will receive their choice (food or money). The reinforcing value of food is scored as the choice (1-16) when money is chosen instead of food. The higher the number associated with the choice of money, the higher the RRV of food. This measure has been shown to be valid and reliable for assessing the RRV of food [60].

#### Reward Task

Participants complete a version of the task described by Gehring and Willoughby [61] in which they choose between 2 monetary options (target stimuli) on each trial and then receive feedback indicating whether the choice resulted in winning or losing money on that trial. In this task, the target stimuli are 2 adjacent squares, each enclosing a number (5 or 25) representing a monetary value (in US cents). These stimuli remain on the screen until a choice is made between the left and right squares. Feedback stimuli follow the choice indicating the outcome of the participant’s decision, that is, the chosen box turns either red or green to signify either a win or a loss (with red or green as the winning color counterbalanced across participants), and the unchosen box turns the other color (either green or red) to indicate what the outcome of the trial would have been had that box been chosen. The feedback stimulus appears for 1000 milliseconds, followed by a blank screen for 1500 milliseconds preceding the onset of the next trial. All 4 possible combinations of 5 and 25, (ie, 5-5, 5-25, 25-5, and 25-25) are evenly crossed with the 4 possible win or loss outcomes (ie, win-win, win-loss, loss-win, and loss-loss), resulting in 16 trial types; thus, although the participant’s choice produces a designated outcome on each trial, signaled by the feedback, outcomes on future trials are not predictable from outcomes associated with prior choices (analogous to a roulette wheel or slot machine). Two sets of these 16 trial types, ordered randomly, are included in each block. Upon completion of a block, participants will receive feedback about their win or loss ratio within that block. The feedback received by the participant will elicit both a feedback-related negativity (FRN) and a reward positivity (RewP) when coupled with an EEG. The amplitude of the FRN largely indexes the relative loss presented in the feedback (ie, FRN amplitude is greater for trials where the participant loses 5 when the alternative was to gain 25 compared with losing 5 when the alternative was to gain 5). The amplitude of the RewP indexes the relative gain (ie, reward) presented in the feedback (ie, the RewP amplitude is greater in trials where the participant gains 25 when the alternative was to lose 25 compared with gaining 25 when the alternative was to lose 5). Extracting the underlying FRN theta (3-9 Hz) and RewP delta (<3 Hz) time-frequency power better measures these processes than amplitude alone.

#### EEG and rTMS Procedures

##### EEG Collection

For the EEG collection, participants are fitted with an elastic cap with embedded electrodes. These electrodes, once they are filled with gel, passively measure electrical brain signals during tasks at a very high resolution (5000 Hz). This high temporal resolution is the key advantage of an EEG as a measure, which produces robust and reliable brain measures across clinical populations. Measures will be collected using a BrainAmp MR Plus 64-channel electrode system (Brain Products GmbH) following standard manufacturer procedures. During data collection, participants will be seated in a comfortable chair 60 cm from the computer screen with access to a button-response box to perform the reward task.

##### rTMS Sessions

The rTMS sessions will be administered using a MagPro X100 including MagOption (MagVenture, Inc) stimulator equipped with a figure-eight coil. All sessions will be completed in the same laboratory that contains the EEG system used in this study [62]. During the rTMS sessions, participants will be seated comfortably in a chair and place their head on a chin rest for stabilization. Reducing head movement is essential for accurately placing and holding the rTMS coil during rTMS applications. Two separate coils that are similar in appearance and acoustic properties are available. One active unblinded coil will be used to determine the resting motor threshold (RMT); the other coil will be blinded (1 side active and 1 side sham) and used to deliver rTMS. The coils are calibrated quarterly against one another to ensure comparable output. Participants will be monitored throughout the study via staff interactions and a monitoring questionnaire assessing typical rTMS side effects (eg, headache).

After the scalp position closest to the motor representation (ie, the *motor hot spot*) is found, the RMT at this location will be determined. Using repeated single pulses, the coil will be moved to determine the optimal scalp position for producing visible contralateral movement in the first dorsal interosseous in the right hand. Pulses over this motor cortex location will be administered to identify the RMT using parameter estimation by sequential testing software [63]. The hot spot located during the initial rTMS session (study visit 1) will be saved in the neuronavigation system (Localite GmbH) and verified at the subsequent session (study visit 2), whereas the RMT will be measured from the hot spot at every session. In accordance with manufacturer instructions and accepted standards, hand motor cortex will be stimulated to obtain the RMT [64-66]. As the l-dlPFC is the target, the left hemisphere (right hand) will be used to determine the RMT.

The l-dlPFC will be targeted using the neuronavigation system (Localite GmbH) Montreal Neurological Institute coordinates (−50, 30, 36) thought to modulate the circuit implicated in reward processing. Over 2 sessions, participants will receive excitatory and sham rTMS sessions once in a single-blind fashion. Excitatory rTMS will consist of intermittent theta-burst stimulation parameters that include 3 pulses given at 50 Hz repeated every 200 milliseconds for a 2-second duration followed by 8 seconds of no stimulation. This sequence will be repeated for a total of 20 cycles, lasts 192 seconds, and delivers 600 pulses [67]. Magnetic field intensity will be set at medium intensity, gradually increasing to the goal of 100% of the participant’s measured daily RMT.

The coil will be set accordingly (active vs sham) for each study day with the order counterbalanced within participant. The blinded coil has 2 sides that can be placed on the participant’s head: 1 side active and 1 side sham (with shielding). These sides look identical to the research staff and the participant, but rTMS pulses are delivered only from the active side. The sham side of the coil is designed to mimic the auditory feedback and scalp pressure evoked by the active side of the coil. The MagVenture system also includes electrodes to be placed on the scalp, near the rTMS stimulation target. This scalp stimulation from the electrodes mimics rTMS administration (ie, causes similar discomfort) but does not modulate brain circuits as rTMS does, thus increasing the likelihood of maintaining the blind without affecting neural signals. The MagVenture sham system is the best commercially available system and can effectively mimic the discomfort of an active rTMS session. To avoid placebo effects, it will be emphasized to the participants that the sensation they feel is related to the stimulation of scalp nerves and muscles and that brain stimulation itself cannot be felt. Such procedures are effective in establishing these sham procedures [68]. Although the aforementioned efforts are taken to preserve the blind, it is possible that the participant will become unblinded to the condition during the study; therefore, a questionnaire assessing the blind and the pain felt will be administered to participants at the end of the study.

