**Objective:**

The goal of the *Transcranial Magnetic Stimulation to Reduce the Relative Reinforcing Value of Food (RESTRAIN)* study is to perform an initial rTMS test on the relative reinforcing value (RRV) of food (the reinforcing value of palatable food compared with money) among adult patients who are pursuing MBS and report high food reinforcement. Using a within-participants sham-controlled crossover design, we will compare the active and sham rTMS conditions on pre- to posttest changes in the RRV of food (primary objective) and the neural modulation of reward, measured via electroencephalography (EEG; secondary objective). We hypothesize that participants will show larger decreases in food reinforcement and increases in brain reward processing after active versus sham rTMS.

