### Design and Procedure Overview

A single-blind, within-participants, sham-controlled study is being conducted to perform an initial test of rTMS on the RRV of food, using a behavioral choice paradigm, and the neural modulation of reward, using an EEG (Figure 1).

Participants will attend 2 study visits that are separated by a washout period of at least 1 week (up to 4 weeks). Participants will receive active rTMS on 1 day and sham rTMS on the other day using a randomized and counterbalanced schedule. Participants will arrive at the laboratory fasted by 8 AM where they are asked to provide a urine sample for drug and pregnancy screening, complete an alcohol breath test, have their height and weight measured, and consume a standardized breakfast. During breakfast, participants will complete demographic, health history, and clinical behavioral and psychological questionnaires. After consuming breakfast, participants will complete a small sampling of 4 different palatable snack foods to determine which food will be used for the RRV measure for both study days. Participants will then complete the RRV measure and a reward task while an EEG is collected before rTMS (pre-rTMS EEG), receive rTMS, and complete the RRV measure and reward task again while an EEG is collected after rTMS (post-rTMS EEG). These procedures will allow for the comparison of pre- to posttest changes in the behavioral (RRV) and neural (EEG) modulations of reward between the active and sham rTMS conditions. Study procedures will be identical across study visits and conditions, except for certain baseline measures on the first day and the within-participant manipulation of active versus sham rTMS administration. A telephone follow-up to assess post-rTMS symptoms will be scheduled after the completion of each visit.

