### Statistical Analysis Plan

The statistical analysis will be conducted using Stata 18 (StataCorp LLC). All continuous measures will first be assessed for their distribution characteristics through the use of Shapiro-Wilk tests and the construction of histograms to determine whether assumptions are met for parametric analysis; if not, nonparametric alternatives will be used. Baseline clinical and demographic characteristics of participants will be assessed using descriptive statistical measures of central tendency and dispersion: means and SDs for those variables meeting assumptions for parametric analysis and medians, range, and IQRs for those not meeting assumptions. The primary outcome of changes in RRV (scores after rTMS−scores before rTMS) for both the active and sham conditions will be computed. Tests comparing the pre-post differences for the active and sham rTMS sessions will be conducted using 2-tailed paired *t* tests (if distributions are normal) or Wilcoxon signed rank tests if the assumptions of distribution are not met).

The EEG data, once collected, will be imported into the MATLAB platform (The MathWorks, Inc) for processing. Data will be filtered offline at 0.1 to 30 Hz and epoched (1000 ms before feedback to 2000 ms after feedback) to capture the FRN and RewP time windows and allow for time-frequency analyses (ie, reducing edge effects). Established preprocessing methods (eg, eye-blink correction, additional filtering, and bad-channel identification) will also be applied. Both theta (3-9 Hz) and delta (<3 Hz) power will be extracted and a principal component analysis applied. This data-driven approach helps separate meaningful segments of the time-frequency surface related to the FRN and RewP components. EEG data will be used to determine differences between active and sham rTMS on the neural modulation of reward [62,70,71]. Pearson and Spearman correlational coefficients will be used to evaluate the associations of clinical assessment measures with RRV and task-specific neural measures (eg, correlation between food craving scores and neural activation related to reward processing). We will control for any differences in hunger and fullness ratings before each RRV task in analyses examining changes in RRV.

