We do not anticipate any period effects (ie, when the outcome of interest changes with time irrespective of treatment effect) because the condition of the treatment is stable for both active and sham rTMS. Regarding carryover effects, we anticipate that the effect of a single session of rTMS will last no more than 24 hours (the washout period is >5 times the anticipated duration of effects).

Regarding participant and rTMS operator ratings of active versus sham rTMS, we will report descriptive data on the percentage of participants and operators who correctly identified the active condition. Such reporting on the success of blind manipulation is standard in the rTMS field.

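### The single-blind label does not fit the staff-masking features the article describes, and as stated it does not keep the condition hidden while the secondary EEG outcome is processed

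*Protocol article*

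**What the plan says.** The masking level appears in two places in the protocol article. Design and Procedure Overview states: "A single-blind, within-participants, sham-controlled study is being conducted". The rTMS Sessions section repeats it for delivery: "Over 2 sessions, participants will receive excitatory and sham rTMS sessions once in a single-blind fashion".

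Other statements bear on what staff can know:

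- rTMS Sessions calls the delivery coil blinded, with one active and one sham side, and adds: "These sides look identical to the research staff and the participant, but rTMS pulses are delivered only from the active side".
- The same section says of the condition: "The coil will be set accordingly (active vs sham) for each study day with the order counterbalanced within participant". It does not say who does the setting.
- Study Visits describes a blind check at the end of visit 2 for the participant only. rTMS Sessions likewise plans its end-of-study questionnaire on the blind for participants.
- Statistical Analysis Plan, however, says: "we will report descriptive data on the percentage of participants and operators who correctly identified the active condition".

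The Abstract names EEG-measured neural modulation of reward as the secondary objective and predicts larger increases in brain reward processing after active than after sham rTMS. The Statistical Analysis Plan section fixes an offline filter of 0.1 to 30 Hz, the epoch limits and the theta and delta bands. It then adds: "Established preprocessing methods (eg, eye-blink correction, additional filtering, and bad-channel identification) will also be applied". A principal component analysis (PCA) follows, described as data-driven, to separate the parts of the time-frequency surface that relate to FRN and RewP.

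**The concern.** A masking statement tells the reader which parties could have influenced the result while knowing the condition. Here the label and the described features give different answers. A reader who relies on the label takes staff to be unmasked. A reader who relies on the coil description and the operator guesses takes the operator to be masked. Neither reading settles the position of the person who sets the coil or the person who processes the EEG.

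The EEG processor matters because the secondary outcome is not read straight off an instrument. Which channels are dropped, what further filtering is applied, and which components are labelled FRN or RewP can all change the theta and delta power that is compared. If such choices are made with the condition visible and a directional hypothesis in mind, they can differ between active and sham sessions. A reader could not then separate that difference from a neural effect. The pilot's effect estimates are also meant to inform the sample size of a later trial, so a distorted estimate would carry forward.

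**Working it through.** The plan gives no figure on this point, so there is none to reproduce. The check is a comparison of statements.

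**Step 1: what the label covers.** Single-blind promises masking of one party. The article attaches the phrase to how participants receive the sessions, and both descriptions of the blind questionnaire concern participants. The masked party under the label is therefore the participant.

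**Step 2: what the other features imply, by role.**

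- *Participant:* masked under the label, supported by the sham coil, scalp electrodes and blind questionnaire. Consistent.
- *Operator:* outside the label. But the sides look the same to research staff, and operators' correct identification of the active condition is to be reported. That report makes sense only if operators are meant not to know. Inconsistent with the label.
- *Person who sets the coil:* someone must arrange active or sham for the day. Neither the role nor its separation from other duties is stated.
- *EEG processor:* not covered by the label, and not covered by the coil features, which act only during stimulation. Not stated.

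**Step 3: the blind check.** Study Visits and rTMS Sessions collect guesses from participants. The Statistical Analysis Plan section reports guesses from participants and operators. The collection of operator guesses is not described where the check is set out.

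**Step 4: where discretion remains in the EEG steps.** Filter band, epoch and frequency bands are fixed. Bad-channel identification, the open-ended extra filtering, and the decision on which PCA segments represent FRN or RewP have no stated rule. The decomposition itself is data-driven, but assigning its components to FRN or RewP is a further step.

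**Step 5: scale.** The number of recordings follows from the design: 2 visits × 2 time points × 10 participants = 40. The size of any processing bias does not follow from anything in the article.

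For orientation only, assume a two-sided 5% paired t test on the EEG change scores with n = 10. The article specifies paired tests for RRV and states no alpha. Assume also a systematic bias of δ standard deviations of the paired difference and no true effect. The rejection rate is P(|T| > t₀.₉₇₅,₉), where T is noncentral t with 9 df and noncentrality δ√10:

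- δ = 0: 5.0%
- δ = 0.1: 5.9%
- δ = 0.2: 8.8%
- δ = 0.3: 13.6%
- δ = 0.5: 29.3%

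Every δ above is an assumption. The list shows that the consequence runs from negligible to serious depending on a quantity the documents do not give. It is not an estimate of bias in this trial.

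**The case against.** The strongest reply is that this rests on silence. No statement says that the EEG processor, or any other member of staff, knows the condition. The masking of processors, bad-channel criteria and component-retention rules are details that a journal article often leaves to the full protocol or analysis plan, and neither is shown. The preprocessing is called established and the PCA data-driven, several settings are already fixed, and blink correction and channel detection may be algorithmic. Any bias would also have to differ between active and sham after the pre-to-post subtraction. And this is a secondary outcome in a proof-of-concept pilot.

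Much of this stands. Missing pipeline detail is not a finding on its own. A reader might infer from the label that staff process the EEG knowing the condition. The documents do not support that, and the identical coil sides and reported operator guesses point towards masked operators. A reader might also infer that the cleaning is done by hand and by eye, which the article does not say.

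Two things survive. The masking level is something the article does state, twice, and it conflicts with features the article also states. And the features that point to masked staff concern the stimulation session. They offer no protection when files are processed later.

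**Conclusion.** The point holds in a limited form. The single-blind label and the operator-masking features contradict each other and need to be reconciled. Under the masking as stated, nothing prevents the secondary EEG outcome from being processed with the condition visible, and some of the processing choices are open.

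Size and direction of any resulting bias are unknown. The conclusion rests on two readings: that single-blind here means the participant, and that at least one of the open EEG choices is not fully automatic.

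Two stronger claims should not be drawn. One is that a few processing choices would decide the result: no figure in the documents supports that. The other is that the primary outcome shares the problem. The RRV score is the choice number at which the participant selects money, so its scoring leaves little room for judgement and needs no added masking on this ground. This is a correction that should be made because it is nearly free. It is not a fault that invalidates the trial.

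**What to change.** 1. State the masking by role in one place: participant, rTMS operator, the person who sets the coil, and the EEG processor. Make the label in Design and Procedure Overview and rTMS Sessions agree with it. Align the description of the blind check with the Statistical Analysis Plan section on whether operators are asked.
2. Store each EEG recording under a code that hides the condition, with the allocation key held by someone who does not process EEG.
3. Do all cleaning, and one PCA pooled over both conditions and both time points, under those codes.
4. Lock the channels, filters and retained FRN and RewP components, with a dated record, before the key is joined for the active-sham comparison.

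The cost is file renaming and a held-back key, with no new participants, visits or procedures. The drawback is that the condition comparison cannot be looked at until processing is locked. The Results section places the analysis in February 2024, after publication, so existing recordings could still be coded before then.
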